### Statistical analysis plan

The primary endpoint will be analysed by intention to treat using a linear mixed-effects model accounting for repeated measures. Values of cap thickness will be entered as the dependent variable. The visit, the treatment group and their interaction will be entered as fixed effects, whereas the patient identification is entered as random effect. Thus, the coefficient of the term accounting for the interaction between the treatment group and visit provides an adjusted estimate of the magnitude of change in thickness at 1 year attributable to the effect of the intervention. The 95% confidence interval of this estimate will be assessed by asymptotic and bootstrap methods. Under a missing at random assumption, this method gives unbiased estimates of the effect. Quantitative indices of endothelial function, coronary physiology and additional metrics of plaque composition will be also analysed using linear mixed-effects models. The analysis of clinical outcomes will be conducted using the Kaplan-Meier method and the log-rank test to compare both intervention groups. Statistical comparisons will be 2-tailed and a statistical significance level of 0.05 shall be considered. Uni- and multivariate linear and non-linear mixed and regression models, adjusting for covariables, will be conducted for the relationship of microbiota composition (diversity and abundance metrics), the number and type of immune cell populations, proteins and metabolites and diet and clinical outcomes.

A modified intention-to-treat analysis including all randomized patients who undergo the catheterization procedure at a 12-month follow-up visit will be used to evaluate the primary endpoint and all secondary endpoints (*intention-to-treat analysis set*). In addition, a per-protocol analysis will be performed following recent directions for analyses of pragmatic trials to control for confounding [42] after excluding from the intervention arm those patients in whom the food frequency questionnaires and biological markers indicate low compliance to the prescribed MedDiet (*per-protocol set*). Secondary endpoints #4–10 will be analysed in all patients that complete the 12-month follow-up period regardless if they undergo the follow-up catheterization procedure or not (*full analysis set*).

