#### Control group

For ethical reasons, in patients allocated to the control group (standard of care), MedDiet is being recommended as part of the secondary prevention programme that all patients receive after an ACS. Diet recommendations are included in the hospital discharge report, focused on the advantages of the currently used Spanish MedDiet eating pattern. Briefly, the Spanish MedDiet eating pattern also emphasizes the consumption of olive oil, wheat, wine, fresh fruits, vegetables, nuts, rice, legumes and fish and seafood; limited consumption of meat and dairy products; and very limited consumption of cream, butter or margarine sugary drinks, baked goods, industrial pastries and pre-cooked foods or dishes. Although these recommendations are common to both intervention arms, previous evidence demonstrates that in the absence of intensive interventions compliance is limited [33]. Thus, significantly different dietary outcomes are anticipated between the two groups.

Implementing standard-of-care diet recommendations or the MedDiet advice does not require alteration to usual care pathways, including the use of any medication, and these will continue for both trial arms.

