**Fig. 2 Fig2:**
[figure not shown]
The MEDIMACS schedule of enrolment, intervention, assessments and endpoints in accordance with the SPIRIT guideline

All patients undergo a complete clinical evaluation at baseline and at 3, 6, 9 and 12 months including a careful assessment of classical cardiovascular risk factors (blood pressure, lipid profile, glycaemic control, medication and alcohol and tobacco consumption). In each visit, the New York Health Association functional class, angina symptoms and major cardiovascular events (cardiac death, need for coronary revascularization and hospital admission for acute coronary syndrome) are recorded. In both groups, the food frequency questionnaire (FFQ) and the Mediterranean Diet Adherence Screener (MEDAS—see below) dietary screener are filled, as well as exercise, nitrate consumption and dental hygiene questionnaires are completed at baseline and at 12 months. In the intervention group, these questionnaires are also completed at the 3-, 6- and 9-month follow-up visits. At the end of the 12-month follow-up period, patients will undergo a repeated intracoronary procedure with measurements of optical coherence tomography (OCT) and endothelial function in the target lesion (see Additional file 2). All patients are sampled for blood, urine, saliva, lingual scrapping and whole faeces at enrolment and at 3, 6, 9 and 12 months. Samples are processed and stored at −80 °C for determination of immune status, protein and metabolite profiles and oral and gastrointestinal microbiota (see Additional file 2).

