### Sample size

The sample size of the MEDIMACS clinical trial has been calculated on the assumption of an expected difference of 40% on the relative change in the fibrous cap thickness of the atherosclerotic plaque from baseline to 12 months between patients undergoing a high-intensity MedDiet intervention in comparison with the standard of care. This magnitude is a 10% lower than the difference previously reported using a similar design in a clinical trial comparing the effect on the fibrous cap of lipid-lowering therapy with 5 mg/day versus 20 mg/day atorvastatin, with an estimated standard deviation of 58% [37]. Based on a two-sample bilateral alpha error of 0.05 and a power of 0.80, the required number of patients is 35 per group. Assuming an attrition rate of 10%, 100 patients are needed to be randomized following a 1:1 allocation ratio. With this sample size, different scenarios could be contemplated under potential deviations from the expected effect size (Table 2).

**Table 2 Tab2:** Alternative scenarios for statistical power with *n* = 100 sample size, assuming 10% attrition rates

Effect size	Power	Comment
50%	100%	Effect addressed in EASY-FIT Study
**40%**	**99.60%**	**Baseline assumptions**
30%	93.45%	Effect 25% relatively lower than expected

Regarding the suitability of this sample size to evaluate the secondary endpoints, micro- and macrovascular endothelial functions are proven to be highly sensitive to detect meaningful effects using small sample populations (50–100 patients) [38, 39]. Microbiota, immunological and metabolic changes in response to diet interventions have been widely reported using small sample populations (20–50 patients), particularly under pathological conditions [40, 41].

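### The primary mixed model carries no baseline lipid covariate, which gives up a modest, nearly free gain in precision

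*Protocol article*

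**What the plan says.** The Statistical analysis plan section of the protocol article writes the primary model out in full: "The visit, the treatment group and their interaction will be entered as fixed effects, whereas the patient identification is entered as random effect". Cap thickness is the dependent variable, and the group-by-visit coefficient is the diet effect. Covariate adjustment is mentioned later in that section, but only for models relating microbiota, immune cells, proteins and metabolites to diet and clinical outcomes. Under Randomization, the only stratification factors are sex and age.

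Three other places bear on the point:

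- The Sample size section takes its planning effect from a trial "comparing the effect on the fibrous cap of lipid-lowering therapy with 5 mg/day versus 20 mg/day atorvastatin". Table 2 gives that trial's effect as 50%. The diet effect planned for is an "expected difference of 40% on the relative change in the fibrous cap thickness".
- The section on participant timeline and assessments has a clinical evaluation at baseline and at 3, 6, 9 and 12 months that covers "lipid profile, glycaemic control, medication and alcohol and tobacco consumption".
- The Control group section leaves usual care unchanged, "including the use of any medication, and these will continue for both trial arms".

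**The concern.** By the article's own benchmark, cap thickness responds to the intensity of lipid-lowering treatment, and by more (50 points) than is expected from diet (40 points). Patients with an acute coronary syndrome can be expected to differ in whether they were already treated and in their LDL cholesterol. If those differences predict how the cap changes over 12 months, a model without them leaves the predictable part in the residual. The interval for the diet effect is then wider than it needs to be.

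At stake is precision in a small trial. The data needed appear to be largely collected already, so the gain would cost almost nothing.

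**Working it through.** **Inputs from the article (Sample size)**

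- Difference of 40 points in relative change.
- SD of that relative change: 58 points.
- Error rates and group size: "Based on a two-sample bilateral alpha error of 0.05 and a power of 0.80, the required number of patients is 35 per group".
- Evaluable patients: of the 100 to be randomized, 50 go to each arm. Losing 10% of them leaves 45 per arm.

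**The plan's own figure.** n = 2(1.960 + 0.842)² × 58²/40² = 33.0, rounded up to 34; the t-test solution is 33.99. The stated 35 per group is reproduced closely enough.

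**What the model already removes.** With two visits and complete data, the group-by-visit term equals the between-arm difference in mean change. Thickening of the same average size in both arms enters the visit term and cancels. Only differences between patients remain.

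**Assumptions (not in the article).** A binary covariate, treated before admission or not, with share p = 0.3 or 0.5. The difference in relative cap change between the two kinds of patient is s = 25 or 50 points; 50 borrows the article's dose contrast and 25 is half of it. This variation is taken to lie within the SD of 58.

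**Formulas**

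- Share of variance explained: p(1−p)s²/58².
- Unadjusted SE: 58 × √(2/45) = 12.2 points.
- Adjusted SE: √(58² − p(1−p)s²) × √(2/45).
- One-SD chance shift in the unadjusted estimate: s × √(2p(1−p)/45).
- Power: noncentral t, two-sided 0.05.

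| p | s | Variance explained | SE | One-SD shift | Power at 30 | Power at 40 |
|---|---|---|---|---|---|---|
| none | none | 0 | 12.2 | – | 68.0% | 89.9% |
| 0.3 | 25 | 131/3364 = 3.9% | 12.0 | 2.4 | 69.7% | 91.0% |
| 0.5 | 25 | 156/3364 = 4.6% | 11.9 | 2.6 | 70.0% | 91.2% |
| 0.3 | 50 | 525/3364 = 15.6% | 11.2 | 4.8 | 75.2% | 94.1% |
| 0.5 | 50 | 625/3364 = 18.6% | 11.0 | 5.3 | 76.7% | 94.8% |

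In terms of sample size, the gain is 1/(1 − 0.039) = 1.04 to 1/(1 − 0.186) = 1.23, that is 4-23% more patients. The shift column is not a further harm: it is the part of the 12.2-point SE that adjustment takes out.

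**Smaller share.** With p = 0.1 and s = 25, the covariate explains 56/3364 = 1.7%, the SE is 12.1, and power at 30 points is 68.7%.

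**Higher attrition.** The Limitations section gives 45% attrition, which leaves 27.5 per arm. Over p = 0.3-0.5 and s = 25-50, power at 40 points then goes from 70.9% to 72.6-79.5%.

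**Simulation.** For p = 0.5, s = 50 and 45 per arm, the unadjusted analysis gave a mean of 40.0 for a true 40 and 0.0 for a true 0, with type I error 4.9%. Adjustment lowered the SE from 12.2 to 11.1 and raised power at 40 points from 90.0% to 94.4%.

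The power figures here differ from Table 2 (99.60% and 93.45%) because those values come out only with 90 per arm.

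**The case against.** The strongest reply is that nothing in the plan is wrong here. An unadjusted mixed model is valid, randomization follows the baseline imaging, and the confidence interval already allows for chance imbalance. Covariates are a choice, and an adjusted sensitivity analysis could sit in a full analysis plan that is not shown. All of this stands, except that the primary model itself is written out in the article and has no covariate.

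A reader might infer more: that drug-driven thickening biases the diet effect, that a result would reflect lipid therapy rather than diet, or that imaging without a run-in on background therapy is a flaw. The documents do not support these. Average thickening cancels in the interaction, the simulation shows no bias, and enrolment soon after the coronary event is the trial's stated setting.

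The size is also open to challenge, and fairly. No document gives the share treated before admission or how far such patients differ in cap change. The 50-point figure compares two doses, not prior users with new starters, so it is best read as an upper value; 25 is simply half of it. The figures are on the relative-change scale of the sample size, whereas the model uses cap-thickness values, so they do not translate directly into its coefficient. At the design effect of 40 points with 45 per arm, the gain is only 1 to 5 percentage points of power.

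Finally, the article lists medication at baseline but does not say that treatment before admission is recorded apart from treatment begun in hospital.

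**Conclusion.** The point holds as a modest improvement in precision. The primary analysis is unbiased and its type I error is sound. It leaves unused a baseline predictor that the article's own benchmark makes plausible. Within the assumed range (30-50% previously treated, 25-50 points, SD 58, 45 per arm), adjustment is worth 4-19% of the variance, and power at a 30-point effect goes from about 68% to 70-77%. With a 10% treated share and a 25-point difference the gain is negligible. It matters more if follow-up imaging is missing on the scale given under Limitations. The direction of the gain follows from a covariate that predicts change; its size rests on assumed inputs.

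**What to change.** Before unblinding, pre-specify two baseline covariates in the primary model: LDL cholesterol at the baseline evaluation, and lipid-lowering therapy before the index admission (yes/no) as recorded there. Enter each with its visit interaction. A main effect alone shifts both visits equally and does nothing for the change. Confirm first that the case report form separates treatment before admission from treatment started in hospital.

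Keep the unadjusted model as a sensitivity analysis. Report lipid-lowering therapy and LDL by arm at 3, 6, 9 and 12 months descriptively, and do not adjust for them: diet may change LDL, and lipid metabolism is among the secondary objectives, so adjustment could remove part of the effect under study.

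The cost is wording and about four degrees of freedom (two covariates, each with a main effect and an interaction). No new data are needed if the case report form is as described.

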### Outcomes

The primary endpoint of the MEDIMACS trial is the change (from baseline to month 12) in fibrous cap thickness of an intermediate atherosclerotic plaque in a non-culprit vessel (identified as the target lesion), as measured by OCT. OCT allows for a very accurate measurement of fibrous cap thickness, as demonstrated in histological validation studies [35]. Moreover, OCT allows the quantitation of plaque composition, lesion size, thickness of the fibrotic layer, lipid arch, minimal lumen area, calcification, macrophage density and plaque rupture [36]. All measurements of OCT are performed by an external core lab, blinded to the allocated diet group.

Secondary endpoints of the MEDIMACS trial are:

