### Limitations

Complying with basic ethical principles, the control group will receive standard-of-care diet recommendations which include several aspects of the MedDiet. Other alternatives, such as a low-fat diet, are associated with worse outcomes than MedDiet and would not be ethical to implement in a contemporary clinical trial [3]. We recognize that, for the purpose of MEDIMACS, adherence to MedDiet in the control group may blur the effect of the experimental intervention and decrease the power to detect differences between arms. However, it has been demonstrated that a personalized, professionalised and closely monitored high-intensity intervention is highly effective to promote adherence to traditional MedDiet, whereas general recommendations are much less powerful [20]. Therefore, we anticipate that true adherence to MedDiet specifications will be highly different between both groups. Nevertheless, primary and secondary endpoints will be analysed both by intention-to-treat and by a per-protocol basis. For this purpose, ad hoc biomarkers have been implemented and will provide investigators with robust metrics of diet adherence and efficacy.

The primary endpoint of the trial is based on intracoronary imaging, and therefore, an invasive catheterization procedure is required for obtaining this read-out. Because patients may refuse undergoing this second study, a 45% attrition has been pre-specified. A detailed plan to quantify compliance to MedDiet in both arms has been designed, including validated dietary self-reporting questionnaires and biomarkers. Biomarkers of compliance will be measured in random subset of participants from the two arms of the trial as a potential way of accommodating both systematic and random components of measurement error in dietary self-reporting.

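### The primary analysis set drops every patient without a 12-month catheterisation, so the intention-to-treat label and the missing-at-random justification do not fit the analysis that will be run

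*Protocol article*

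**What the plan says.** The first paragraph of the protocol article's Statistical analysis plan states: "The primary endpoint will be analysed by intention to treat using a linear mixed-effects model accounting for repeated measures". Visit, group and their interaction are fixed effects, the patient is a random effect, and the interaction is the treatment estimate. The justification offered is: "Under a missing at random assumption, this method gives unbiased estimates of the effect".

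The second paragraph defines the population: "A modified intention-to-treat analysis including all randomized patients who undergo the catheterization procedure at a 12-month follow-up visit". This set "will be used to evaluate the primary endpoint and all secondary endpoints", and the article labels it the intention-to-treat analysis set. A wider full analysis set is also defined, but only for secondary endpoints 4 to 10, which "will be analysed in all patients that complete the 12-month follow-up period regardless if they undergo the follow-up catheterization procedure or not". The primary endpoint is not among them.

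On measurement, Outcomes states: "The primary endpoint of the MEDIMACS trial is the change (from baseline to month 12) in fibrous cap thickness". Participant timeline and assessments adds: "At the end of the 12-month follow-up period, patients will undergo a repeated intracoronary procedure". On missing data, Limitations states: "Because patients may refuse undergoing this second study, a 45% attrition has been pre-specified". The Sample size section works with 10%.

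**The concern.** A likelihood-based mixed model tolerates data missing at random because patients with an incomplete record stay in the likelihood. With two planned OCT visits, the incomplete record that matters is a baseline value with no 12-month value. The stated set excludes those patients by definition, so the reason given for choosing the model no longer applies to the main source of missing data.

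What is at stake is the primary estimate. If attendance at the second, invasive procedure is related to baseline cap thickness and the net selection differs between arms, regression to the mean shifts the completers' mean change by different amounts in the two arms. Missing at random permits this pattern. The model applied to all randomised patients would handle it, and the model applied to the stated set does not.

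**Working it through.** **Inputs from the protocol article.** Target difference 40 points and SD 58 points on relative change; two-sided alpha 0.05; power 0.80; 35 per group; N = 100; attrition 10% (all from Sample size). Attrition 45% (Limitations). OCT at baseline and 12 months (Outcomes; Participant timeline and assessments).

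**Assumed, because the documents give no figure.** Correlation rho between visits of 0.3 to 0.7; equal variance at both visits; attendance logistic in baseline thickness with log-odds of -0.5 or -1.0 per SD in one arm and no dependence in the other; no true effect. The 58% is treated as the SD of change, although the model itself is fitted to cap thickness values.

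**1. The plan's own figure.** n per group = 2 × (1.960 + 0.842)² × (58/40)² = 33.005, which rounds up to 34. The stated 35 is reproduced to within one patient, so 40 and 58 are the right scale for judging size.

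**2. What the model estimates in the stated set.** With complete pairs, the visit-by-group interaction is (mean 12-month minus mean baseline, intervention) minus (the same, control). In one simulated data set with 60 completers, the mixed model and the plain difference in mean change both gave 25.7636. Keeping the baseline-only patients gave 18.82. The model adds nothing to a completer comparison once those patients are gone.

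**3. Bias formula.** In baseline SD units with no treatment effect, change = -(1 - rho) × baseline + noise. Let d be the mean baseline of attenders in an arm.
- Bias = -(1 - rho) × (d_intervention - d_control).
- SD of change = √(2(1 - rho)).
- On the 58-point scale, absolute bias = 58 × √((1 - rho)/2) × |d_intervention - d_control|.

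**4. Numbers.** The value of d in the arm with selection comes from numerical integration over a standard normal baseline, with the intercept set to give the attrition rate. In the other arm d = 0.

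| Attrition | Log-odds per SD | d | Bias, rho 0.3 | rho 0.5 | rho 0.7 |
|---|---|---|---|---|---|
| 45% | -0.5 | -0.212 | 7.3 | 6.2 | 4.8 |
| 45% | -1.0 | -0.372 | 12.8 | 10.8 | 8.4 |
| 10% | -0.5 | -0.049 | 1.7 | 1.4 | 1.1 |
| 10% | -1.0 | -0.091 | 3.1 | 2.6 | 2.0 |

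Example: 58 × √(0.5/2) × 0.372 = 10.8. Large-sample simulation at slope -1.0 agrees closely (10.7 at 45%, rho 0.5), and the likelihood estimate using all baselines had bias of about 0 in every scenario.

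**5. Milder or no differences between arms (rho 0.5).**
- Slopes of -0.25 and -0.5 in the two arms at 45% attrition: about 3 points.
- The same slope of -0.5 in both arms, but attrition of 55% and 35%: about 3 points.
- The same slope and rate in both arms, or attendance unrelated to baseline: about 0.

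**6. The model at the trial's size.** In 400 simulated trials of 100 patients (about 45% dropout, rho 0.5, baseline SD 30, true interaction 20), slopes were set at 1 in opposite directions by arm to make the effect visible. The completer fit averaged 31.1 and the all-randomised fit 20.0 (Monte Carlo SE 0.4 each). The formula predicts a bias of 0.5 × 2 × 0.372 × 30 = 11.2, and 11.1 was observed. This scenario shows how the two fits behave. It does not estimate the likely size of bias in this trial.

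**The case against.** The strongest reply is that the restriction is disclosed. The second paragraph uses the word modified and defines the set exactly, and Limitations admits that patients may refuse. Patients who are catheterised but have no usable OCT stay in the set, so the missing-at-random sentence keeps some application. All of that stands. It does not help with patients who have no second procedure, and the first paragraph and the set's label still say plain intention to treat.

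A second reply concerns mechanism. A reader might infer that intensive contact in one arm, without blinding of patients, is enough to bias the completers. It is not, because those features argue for different attendance rates. If attendance is unrelated to cap thickness, different rates alone (60% against 30% attrition was checked) give a bias of about 0. OCT is read by an external core laboratory blinded to diet group, and nothing in the article says that patients or staff act on the reading. An indirect link through disease severity is possible but is not documented.

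A third reply concerns size. The slopes, the correlation and the conversion to the 58% scale are all assumed. With about 27 completers per arm the standard error is 58 × √(2/27) = 15.8 points, so even 13 points is less than one standard error. That is a fair limit on how strongly the size can be put, although a systematic shift does not average out as sampling error does.

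**Conclusion.** The inconsistency is established from the text: the stated set removes the baseline-only records on which the stated justification depends. The completers' estimate is unbiased only under a stronger condition than the one given, such as attendance unrelated to baseline thickness, or related to it identically in both arms.

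The size is conditional. Under the one-arm selection assumed above it is about 5 to 13 points at 45% attrition and about 1 to 3 points at 10%, against a 40-point target. It is smaller with milder arm differences and about 0 with none. Which attrition figure applies is itself unsettled, since the article gives both.

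Two stronger readings are not supported. One is that the trial's result will be biased by a known amount: the documents give no correlation, no attendance model and no evidence that thickness drives attendance, and even the direction is unknown. The other is that refitting the model cures attrition bias. With two OCT visits and no further covariates, it corrects only for selection on baseline cap thickness. Refusal driven by symptoms, events or motivation that baseline thickness does not capture remains uncorrected in either set.

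**What to change.** Define the primary analysis set as all randomised patients with an analysable baseline OCT, and fit the planned mixed model to it, using the 12-month OCT wherever it was obtained. Keep the catheterised subset as a sensitivity analysis and call it a completer set. Apply the intention-to-treat and missing-at-random wording only to the first of these. State in one sentence that the analysis does not protect against refusal that depends on factors outside the model.

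The cost is a change of wording and the same model run on more rows. No new data are needed. The Participants section places the intracoronary study before randomisation, so a baseline OCT should exist for nearly everyone. That every one is readable is an inference, which is why the set is defined by an analysable baseline. Recruitment is complete, but this changes only the analysis, and it should be settled before the 12-month data are compared by arm.

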Changes (baseline to month 12) in the minimum luminal area (mm^2^) and intraluminal diameter measured by OCT in the target lesionPresence of anatomic findings related to plaque instability and vulnerability at 12 months identified by OCT in the target lesion (atheroma plaque rupture, erosion or thrombus)Changes (baseline to month 12) in the micro- and macrovascular endothelial function as a marker of early stages of coronary atherosclerosis, measured by a combined flow-pressure guidewire in the target lesion (change in maximum average speed, coronary flow, coronary flow reserve, fractional flow reserve, basal and hyperaemia microvascular resistances, resistance of basal stenosis and hyperaemia, and coronary impedance during the cardiac cycle)Differences between groups in the micro- and macrovascular endothelial function at 12 monthsDifferences between groups in the neointima thickness of the stent in the treated artery (at 12 months)Changes (baseline to month 12) of the immunological status, including innate T and B cell populations (NK, innate lymphoid cells, monocytes/macrophages) and NKT cellsChanges (baseline to month 12) of gene expression of cytokines and epigenetic profiles associated with methylation, histidine decarboxylase and miRNAChanges (baseline to month 12) in the diversity of the T cell receptors using massive sequencing methodologiesChanges (baseline to month 12) of the microbiota abundance and diversity identified using the 16S rRNA massive sequencing approach and the functional analysis of complete metagenomesChanges (baseline to month 12) of the host and microbiota protein and metabolomics profiles using mass spectrometry (MS) and nuclear magnetic resonance (NMR)-based methodsIncidence at 1 year of major adverse cardiovascular events (MACE) defined as cardiovascular death, myocardial infarction or ischemic strokeClinically driven coronary revascularizationKaplan-Meier analysis of MACE (as defined above) and of clinically driven coronary revascularization

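### As worded, the analysis sets for MACE and revascularisation admit only patients who reach month 12, so the between-arm comparison cannot count an earlier death

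*Protocol article*

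**What the plan says.** All references are to the Protocol article.

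- **Main set.** The Statistical analysis plan section defines its main set, a modified form of intention to treat, in these words: "including all randomized patients who undergo the catheterization procedure at a 12-month follow-up visit will be used to evaluate the primary endpoint". The same sentence extends it to every secondary endpoint: the set "will be used to evaluate the primary endpoint and all secondary endpoints". The section labels this the intention-to-treat analysis set.
- **Exception.** "Secondary endpoints #4–10 will be analysed in all patients that complete the 12-month follow-up period", whether or not the repeat catheterisation takes place. This is the full analysis set.
- **Timing of the qualifying procedure.** Participant timeline and assessments: "At the end of the 12-month follow-up period, patients will undergo a repeated intracoronary procedure".
- **Clinical endpoints.** Outcomes lists the one-year incidence of "major adverse cardiovascular events (MACE) defined as cardiovascular death, myocardial infarction or ischemic" stroke, then clinically driven revascularisation, then a Kaplan-Meier "analysis of MACE (as defined above) and of clinically driven coronary revascularization".
- **Method.** "The analysis of clinical outcomes will be conducted using the Kaplan-Meier method and the log-rank test to compare both intervention groups". This sentence names no population of its own.
- **Events noted at visits.** Participant timeline and assessments: "major cardiovascular events (cardiac death, need for coronary revascularization and hospital admission for acute coronary syndrome) are recorded".

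**The concern.** A MACE endpoint that includes death has to be analysed in a population that the dead can belong to. Here, membership of the set is decided by an event about a year after randomisation: being alive for, and accepting, a second invasive procedure. Three things follow if the text is applied as written.

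- The fatal component of MACE is zero up to the month-12 procedure, so event-free survival is overstated.
- Non-fatal events and revascularisations are dropped in anyone who refuses or cannot have the repeat procedure.
- The arms are no longer compared as randomised. The intervention arm has dietitian sessions, monthly calls and free olive oil, and the control arm does not, so acceptance of the procedure could differ by arm. The log-rank comparison could then be biased in either direction.

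**Working it through.** The plan states no figure for this point, so the check is mainly one of logic: number the endpoints, map them to the sets, and see who can enter each set.

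**Step 1. Number the secondary endpoints.** The printed numbers are not visible in the text, so they are counted in list order under Outcomes.

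| # | Endpoint | Needs the 12-month catheterisation? | Set as written |
|---|---|---|---|
| 1 | Luminal area and diameter | yes | catheterised |
| 2 | Plaque instability findings | yes | catheterised |
| 3 | Change in endothelial function | yes | catheterised |
| 4 | Endothelial function at 12 months | yes | full analysis |
| 5 | Stent neointima at 12 months | yes | full analysis |
| 6–10 | Immune status, gene expression, T cell receptors, microbiota, proteins and metabolites | no | full analysis |
| 11 | MACE | no | catheterised |
| 12 | Clinically driven revascularisation | no | catheterised |
| 13 | Kaplan-Meier analysis of 11 and 12 | no | catheterised |

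Two mismatches appear. Endpoints 4 and 5 are exempted from a procedure they cannot be measured without, and 11–13 are tied to a procedure they do not need. Counting the primary endpoint as #1 does not change this: MACE becomes #12, still outside #4–10.

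**Step 2. Can a patient who dies before month 12 be counted?**

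- Catheterised set: no, because the qualifying procedure comes at the end of follow-up.
- Full analysis set: no, because it requires completing 12 months.
- Per-protocol set: no help, because it only removes further patients, from the intervention arm.

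In the catheterised set every patient is under observation until the month-12 procedure. Nobody is censored before then, and the time up to it is free of death by selection (immortal time).

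**Step 3. Size of the set.** Inputs: 100 randomised and 10% attrition (Sample size); 45% attrition, attributed to refusal of the second procedure (Limitations). Patients in the set = 100 × (1 − attrition).

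- 10%: 100 × 0.90 = 90, so about 10 are left out.
- 45%: 100 × 0.55 = 55, so about 45 are left out.

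These are patients, not events.

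**Step 4. Illustration of events lost.** The article gives no MACE rate for this population, so the following are assumptions: *f* first events per 100 that are cardiovascular deaths (2, 5 or 12) and *g* that are non-fatal MACE (5 or 10). The upper value of *f* borrows the 12% six-month mortality after ACS admission quoted under Background. This trial excludes Killip III/IV, so fewer deaths are likely. Other losses are taken as unrelated to events.

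Counted in the catheterised set = *g* × min(1, set size / (100 − *f*)); deaths counted = 0. For example, with *f* = 2, *g* = 5 and 45% attrition: 5 × 55/98 = 2.8.

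| *f* | *g* | All randomised | Counted, 10% attrition | Counted, 45% attrition |
|---|---|---|---|---|
| 2 | 5 | 7 | 4.6 | 2.8 |
| 2 | 10 | 12 | 9.2 | 5.6 |
| 5 | 5 | 10 | 4.7 | 2.9 |
| 5 | 10 | 15 | 9.5 | 5.8 |
| 12 | 5 | 17 | 5.0 | 3.1 |
| 12 | 10 | 22 | 10.0 | 6.3 |

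With 12 deaths the set cannot exceed 88, so the 10% column is capped there. Over the assumed range, 7 to 22 first events in all randomised patients become roughly 3 to 10, none fatal.

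**Step 5. Visit list against definition.** The visit list has cardiac death where MACE has cardiovascular death, and ACS admission where MACE has myocardial infarction. It has no entry for ischemic stroke.

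**The case against.** The best defence is that the numbering is a slip and no one means to discard deaths. It has force. The range #4–10 covers seven items, and exactly seven listed outcomes need no catheterisation (6–12), since item 13 is only an analysis of 11 and 12. A reference shifted by two would fit both the count and the stated purpose. A Kaplan-Meier analysis of an endpoint containing death also makes little sense among survivors only. So a reader might infer a settled decision to ignore deaths, and the article does not support that; it contradicts itself. But the slip does not rescue the analysis: the set to which MACE would move still requires completing 12 months. Nor does the promise under Limitations to analyse endpoints by intention to treat, because the plan gives that label to the catheterised set.

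Three further inferences go too far.

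- *That the trial's safety oversight is compromised.* Adverse outcomes documents all serious adverse events, related or not, and plans a clinical-outcome analysis of the first 50 recruited patients after their 12-month follow-up. Neither is restricted to catheterised patients.
- *That stroke reaches the data only through serious adverse event forms.* The case report form is not shown. What can be said is that the visit list and the MACE definition differ.
- *That 45 events would be lost.* The figure is patients left out, most of whom may have no event, and the article also states 10%.

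It is also fair that the trial is mechanistic, is sized on fibrous cap thickness and claims no power for MACE. The primary endpoint needs the procedure and is untouched by this point.

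**Conclusion.** The point stands as an error in the wording of the analysis sets. Read literally, #11–13 are analysed only in patients who undergo the month-12 catheterisation. Read charitably, they belong to the full analysis set. On neither reading can a death before month 12 enter the between-arm comparison. On the literal reading, 10 to 45 of 100 randomised patients are also left out, depending on which of the article's two attrition figures applies.

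The conclusion rests on counting the list in printed order and on taking completion of 12 months to mean being alive and followed to then. The article offers no other definition. The event counts in the illustration are assumed, not taken from the plan.

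This is a should-fix. The endpoints are secondary and carry no power claim, but with so few events expected, losing even two to five deaths could alter the comparison.

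**What to change.** 1. State that secondary endpoints #11–13 are analysed in all randomised patients by assigned arm, with time running from randomisation to first event, last contact or month 12.
2. Change the exception from #4–10 to #6–10, and keep #1–5 in the imaging set.
3. Reconcile the per-visit event list under Participant timeline and assessments with the MACE definition under Outcomes (type of death, infarction, ischemic stroke).

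Items 1 and 2 cost only wording: no extra patients or procedures are needed, because clinical events are recorded at visits and serious adverse events are documented for everyone. Item 3 is also wording if the case report form already holds the MACE components. If it does not, the missing component would have to be confirmed from serious adverse event records, since recruitment is already complete.
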